**Aim 4: To investigate the association between AVF luminal pressure and known risk factors of AVF maturation failure**

As described above, the suggested risk factors of AVF maturation failure include anemia, advanced age, diabetes mellitus, and smoking.^[18]^ Nonetheless, how these risk factors actually affect AVF hemodynamics remained to be defined. In the present study, these known risk factors of AVF maturation failure and laboratory profiles associated with renal failure will be collected at the time of the AVF creation. The association between calculated luminal pressure and these risk factors will be analyzed. These results will provide novel evidence to support the pathogenic role of the known risk factors of AVF maturation failure.

### Study design and procedure

2.2

This prospective observational study is mainly aimed to investigate the association between AVF luminal pressure and maturation rate. Patients who meet the following eligibility criteria are eligible for enrollment:

1.patient at pre- or post-dialysis status who undergoes surgical creation of native AVF for hemodialysis, and2.AVF created at both radial and brachial arteries.

### Participants

2.3

In the present study, patients scheduled to have AVF will be informed about current limitations of AVF technique and the need to improve AVF maturation rate. Then, we explain how this study will help patients receiving AVF creation in the future and encourage them to participate the study voluntarily. Patients who decide to participate the study will be explaining the time required to complete the measurements. Apart from the above statement, patients/the public were not involved in the study design, development of the outcomes and measurements, or dissemination of the study results.

#### Inclusion criteria

2.3.1

The included participants will receive vascular sonography to measure the diameters, flow rates, and flow volumes of AVF and its branched veins within 1 week from the surgical creation of AVF (Fig. 1).

**Figure 1 F1:**
[figure not shown]
Flowchart of the study design. AVF = arteriovenous fistula.

#### Exclusion criteria

2.3.2

The exclusion criteria are as follows:

1.patients <20 years of age,2.patients who are unconscious or unable to sign the informed consent,3.patient in whom native AVF creation is shifted to arteriovenous graft placement due to technical difficulty.

#### Recruitment

2.3.3

Subject recruitment began in September 2018 at Wan Fang Hospital, Taipei Medical University, Taipei, Taiwan and is expected to end by May 2020. The recruitment of participants, collection of parameters, and confirmation of the outcomes will be performed by a fulltime study nurse.

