#### Laboratory analysis

2.4.2

The laboratory data of pre-surgical evaluation, including hemoglobin and white blood cell count as well as levels of serum urea, creatinine, sodium, potassium, calcium, phosphorus, albumin, and parathyroid hormone will be included as covariates. Before the creation of AVF, pre-procedural vascular sonography of both arms will be performed to determine the optimal site for the AVF. After the creation of the AVF, vascular sonography of the ipsilateral arm will be repeated within 1 week to measure the diameters, blood flow rates, and blood flow volume of the AVF and its main branches as described previously. The AVF luminal pressure will be calculated from blood flow rates using the modified Bernoulli equation as described in the following section.

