#### Estimation of luminal pressure of AVF

2.4.3

For the radiocephalic AVF, the blood flow rates will be measured at the radial artery-to-cephalic vein anastomosis and the site of cephalic vein bifurcation into the basilic and cephalic veins. The luminal pressure in the radiocephalic AVF will be estimated by the pressure gradient from these two points. For the brachiobasilic AVF, blood flow rates will be measured at the brachial artery-to-basilic vein anastomosis and basilic vein-to-brachial vein junction. The luminal pressure of the brachiobasilic AVF will be estimated by the pressure gradient between these two points. For the brachiocephalic AVF, the blood flow rates will be measured at the brachial artery-to-median basilic vein anastomsosis and cephalic vein-to-subclavian vein junction. The luminal pressure of the brachiocephalic AVF will be estimated by a pressure gradient between these two points.

The blood flow rates of the AVF and its branches will be measured by Doppler ultrasound (Zonare Ultrasound System, Shenzhen Mindray Bio-Medical Electronics Co.). All Doppler ultrasound examinations will be performed by 2 rotating technicians to ensure consistency between measurements. Then, the pressure gradient between the arterial and venous ends of the AVF will be estimated using the modified Bernoulli equation as following: 

Where ΔP refers to the pressure gradient, V_1_ refers to the proximal blood flow rate, and V_2_ refers to the distal blood flow rate. The absolute blood pressure of the arterial limb of the AVF will be approximated as the mean arterial pressure of the contralateral arm. Then, the blood pressure of the AVF will be approximated with the following equation: 

Where MAP refers to the mean arterial pressure measured in the contralateral brachial artery.

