### Outcomes

2.5

The primary outcome of this study is spontaneous AVF maturation, which is defined as provision of sufficient blood flow for hemodialysis within 2 months of its creation without any interventional procedures. The secondary outcome is assisted AVF mature, which is defined as AVF maturation within 2 months from its creation, which is aided by any interventional procedure before successful use of AVF. The maturation time is defined as the period from the date of AVF creation to the date of the first successful employment for hemodialysis.

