### Statistical plan

2.6

Continuous variables will be expressed as mean ± standard deviation, while nominal variables are expressed in frequency and percentage. Comparisons of continuous variables will be performed using the 2-tailed *t* test for unpaired samples or Welch *t* test as appropriate. Comparisons of nominal variables will be performed using the Chi-square test or Fisher exact test as appropriate. Multivariate logistic regression test will be used to evaluate the association between predictor variables and outcome variables. Statistical significance will be defined by a *P* value of <.05. The statistics will be performed using SAS 9.4 (SAS Institute Inc, Cary, NC).

G∗Power 3.1.9.4 was used to estimate the sample size to reach statistical significance in the *t* test. Assuming the effect size to be 0.6. Under the condition that α error is defined as 0.05; power was defined as 0.8; and the allocation ratio was defined as 1. Therefore, the sample size required to achieve statistical significance is 90 patients.

The data used for the study will be preserved and analyzed by the primary investigator. The data is accessible only to the primary investigator and study nurse for data safety. The data will be preserved for 2 years after the end of the study.

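### One nurse both collects the study parameters and confirms an outcome with no stated flow threshold, so the week-1 Doppler values could influence how borderline fistulas are classed

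*Protocol article*

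**What the plan says.** The protocol article, section 2.3.3 (Recruitment), assigns three tasks to one role: "The recruitment of participants, collection of parameters, and confirmation of the outcomes will be performed by a fulltime study nurse". Section 2.6 (Statistical plan) adds: "The data is accessible only to the primary investigator and study nurse for data safety".

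The exposure comes first. After surgery, section 2.4.2 (Laboratory analysis) says, "vascular sonography of the ipsilateral arm will be repeated within 1 week to measure the diameters, blood flow rates, and blood flow volume". The nurse does not make these measurements. Section 2.4.3 (Estimation of luminal pressure of AVF) says: "All Doppler ultrasound examinations will be performed by 2 rotating technicians to ensure consistency between measurements". Pressure is then calculated by formula; the article does not say by whom or when.

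The primary outcome in section 2.5 (Outcomes) is "provision of sufficient blood flow for hemodialysis within 2 months of its creation without any interventional procedures". No flow figure is attached. The same section dates maturation to the "first successful employment for hemodialysis" and does not define success. Section 2.2 (Study design and procedure) admits any "patient at pre- or post-dialysis status who undergoes surgical creation of native AVF for hemodialysis", so some participants may have had no dialysis session by two months.

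**The concern.** Four stated features combine. The person who confirms the outcome also collects the parameters and may see the data. The Doppler readings exist up to two months before the outcome is classed. The outcome depends on a term with no threshold. The Abstract declares a direction, that higher pressure is harmful.

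If a borderline fistula is more readily called a failure when its week-1 values look unfavourable, the misclassification is tied to the exposure. Random misclassification tends to dilute an association; this kind can create one. It would fall on Aim 3, the association between luminal pressure and maturation, which is the study's main question.

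**Working it through.** **Step 1: the plan's own figure.** Inputs from section 2.6: effect size 0.6, α = 0.05 (two-tailed), power 0.8, allocation ratio 1.

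- Normal approximation: n per group = 2 × (1.960 + 0.842)² / 0.6² = 2 × 7.85 / 0.36 = 43.6, rounded up to 44, or 88 in total.
- Noncentral t, as G\*Power uses: 44.59, rounded up to 45 per group, or **90** in total, with power 0.804.

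The stated 90 is reproduced and is not in dispute.

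**Step 2: how far pressure-linked classing could move the t test.** Simulation with no true effect, 20,000 studies per setting:

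- N = 90 (section 2.6).
- Maturation 65%, varied from 50% to 80%, the range quoted in the Introduction.
- Pressure drawn as standard normal, independent of maturation.
- A share f of outcomes is borderline. **This share is an assumption; the article gives no figure for it.**
- Every borderline fistula is recorded as matured if its pressure is below the median and as failed if above. This is also an assumption, and the extreme one.
- Two-sided t test at 0.05.

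| Borderline share f | Patients (f × 90) | Rejection, 65% maturation | Rejection, 50% to 80% maturation | Spurious difference at 65% (SD) |
|---|---|---|---|---|
| 0% | 0 | 5% | 5% | 0 |
| 5% | 4.5 | 7% | about 7% | 0.09 |
| 10% | 9 | 12–13% | 12–14% | 0.17 |
| 15% | 13.5 | 22% | 20–26% | 0.26 |
| 20% | 18 | 35% | 33–41% | 0.35 |

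At f = 20% the spurious difference is 0.35 / 0.6 = 58% of the effect size the study was planned to detect.

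**Step 3: relaxing the extreme assumption (65% maturation).**

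- Only 75% of borderline calls follow pressure: rejection is 7–9% at f = 10%, 9–14% at 15% and 12–22% at 20%. The lower ends apply if the other quarter go against pressure, the upper ends if they are recorded at their true status.
- Borderline fistulas are called matured when pressure lies in the middle half of its distribution: rejection stays between 5% and 6%, even at f = 20%. A non-linear analysis could still be affected.
- 20% of outcomes misjudged at random: rejection is 4.8%.

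The harm therefore comes from the link to pressure and not from misjudgement as such.

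**The case against.** The strongest reply is that the arrangement is less exposed than it looks. Section 2.3.3 speaks of parameters, not pressure. Technicians make the Doppler measurements. If pressure is calculated only at analysis, the nurse never holds a pressure value when classing the outcome. The direction is also less settled than the Abstract suggests: the Introduction and section 2.1 (Main aims) seek an optimal range, with some elevation required and excess harmful, so there is no agreed unfavourable value to lean towards. The step 2 figures assume full adherence to a median that nobody would know while the study is running. And a condensed article need not describe masking.

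Much of this stands. The route is knowledge of the readings, not measurement by the nurse, and the figures are upper bounds for each borderline share. Silence about masking is not the point. What remains is stated in the text: one person has both tasks and data access, and the outcome term has no threshold. Early flow readings could also sway a judgement about sufficient flow without any pressure being calculated.

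A reader might also infer that clinicians act on week-1 pressure, so that an intervention it prompts makes the fistula a primary-outcome failure. The documents do not support this. They nowhere say that treating clinicians receive or act on pressure, and section 2.6 restricts data access. For the nurse, whether a procedure took place is mostly a recorded fact.

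**Conclusion.** The concern holds as a risk built into the stated roles and outcome definition. It is not a demonstrated bias. Its size cannot be derived from the documents. With no true effect, 90 patients and 65% maturation, the false-positive rate is at most about 7% if 5% of outcomes are borderline, and at most about 35% if 20% are. Those ceilings assume that every borderline call follows a median split of pressure; partial adherence lowers them, and favouring mid-range pressure leaves the t test close to its nominal level. If pressure is already calculated after outcomes are confirmed and the nurse does not see the readings, the risk is small and the article need only say so.

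Two further inferences go too far: that the nurse measures or necessarily knows the luminal pressure, and that the resulting error would be beyond any later remedy. The documents establish neither.

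**What to change.** For patients whose outcome is not yet confirmed, amend sections 2.3.3, 2.5 and 2.6 as follows:

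- The technicians' week-1 study readings are stored without being shown to the nurse, and the data-access statement is changed to match. Withholding calculated pressure alone would leave the raw readings in view.
- The investigator calculates the gradient and luminal pressure only after the patient's two-month outcome has been entered and locked.
- The nurse classes the outcome from dialysis-session and procedure records, against a measurable definition of sufficient flow and successful use that the sponsor fixes beforehand. The definition should say how patients not yet on dialysis are classed.
- The ordinary clinical scan report stays available for care. Masking is therefore not complete, and the nurse should not consult that report when classing the outcome.

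This needs no extra staff, visit or procedure, and the sample size stays at 90. The cost is a change in the order of data entry and calculation, with pressure values available about two months later. Recruitment began in September 2018 and the article appeared in October 2019, so patients already past two months may not be covered. The report should state how many outcomes were confirmed before the change.

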### Variables

2.4

#### Demographic variables

2.4.1

The demographic profiles of the included patients, including gender, age, body mass index, smoking status, and culprit disease of renal failure will be documented. Comorbidities including diabetes mellitus, hypertension, coronary artery disease, peripheral arterial occlusion disease, atrial fibrillation, and related medication will be recorded.

#### Laboratory analysis

2.4.2

The laboratory data of pre-surgical evaluation, including hemoglobin and white blood cell count as well as levels of serum urea, creatinine, sodium, potassium, calcium, phosphorus, albumin, and parathyroid hormone will be included as covariates. Before the creation of AVF, pre-procedural vascular sonography of both arms will be performed to determine the optimal site for the AVF. After the creation of the AVF, vascular sonography of the ipsilateral arm will be repeated within 1 week to measure the diameters, blood flow rates, and blood flow volume of the AVF and its main branches as described previously. The AVF luminal pressure will be calculated from blood flow rates using the modified Bernoulli equation as described in the following section.

#### Estimation of luminal pressure of AVF

2.4.3

For the radiocephalic AVF, the blood flow rates will be measured at the radial artery-to-cephalic vein anastomosis and the site of cephalic vein bifurcation into the basilic and cephalic veins. The luminal pressure in the radiocephalic AVF will be estimated by the pressure gradient from these two points. For the brachiobasilic AVF, blood flow rates will be measured at the brachial artery-to-basilic vein anastomosis and basilic vein-to-brachial vein junction. The luminal pressure of the brachiobasilic AVF will be estimated by the pressure gradient between these two points. For the brachiocephalic AVF, the blood flow rates will be measured at the brachial artery-to-median basilic vein anastomsosis and cephalic vein-to-subclavian vein junction. The luminal pressure of the brachiocephalic AVF will be estimated by a pressure gradient between these two points.

The blood flow rates of the AVF and its branches will be measured by Doppler ultrasound (Zonare Ultrasound System, Shenzhen Mindray Bio-Medical Electronics Co.). All Doppler ultrasound examinations will be performed by 2 rotating technicians to ensure consistency between measurements. Then, the pressure gradient between the arterial and venous ends of the AVF will be estimated using the modified Bernoulli equation as following: 

Where ΔP refers to the pressure gradient, V_1_ refers to the proximal blood flow rate, and V_2_ refers to the distal blood flow rate. The absolute blood pressure of the arterial limb of the AVF will be approximated as the mean arterial pressure of the contralateral arm. Then, the blood pressure of the AVF will be approximated with the following equation: 

Where MAP refers to the mean arterial pressure measured in the contralateral brachial artery.

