**Aim 1: To characterize the altered blood flow rates and luminal pressures in different segments of AVF**

While excessive AVF luminal pressure may stimulate the proliferation of AVF venous subintima to cause maturation failure, comprehensive AVF hemodynamic profiles in different AVF segments should be characterized first. In this study, the blood flow rates will be measured at the artery-to-vein anastomosis, the bifurcation sites of AVF, and its branches after bifurcation. With these flow rate values, the pressure gradient across the AVF will be calculated. We will also estimate the absolute AVF luminal pressure using the difference between the mean arterial pressure and AVF pressure gradient. These results will provide a comprehensive hemodynamic profile of AVF and may reveal novel and valuable risk factors of AVF maturation failure.

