**Aim 3: To investigate the association between AVF luminal pressure and AVF maturation rate**

The pressure gradient and absolute luminal pressure in AVF will be calculated using the blood flow rates in different sites of the AVF. With these results, the association between pressure values and AVF maturation rates will be analyzed. These results may improve our understanding about the role of AVF luminal pressure at maturation. Moreover, valuable and modifiable risk factors for AVF maturation failure may be disclosed, which may be manipulable surgically or pharmaceutically in future.

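### Rotating two technicians does not by itself make the Doppler readings consistent; record the technician and carry it into the Aim 3 model

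*Protocol article*

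**What the plan says.** Section 2.4.3 of the protocol article describes the Doppler measurements and gives a reason for the staffing: "All Doppler ultrasound examinations will be performed by 2 rotating technicians to ensure consistency between measurements".

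These readings produce the study's exposure. Section 2.4.2 says "The AVF luminal pressure will be calculated from blood flow rates using the modified Bernoulli equation", and section 2.4.3 defines the two inputs as a proximal and a distal reading (the first "refers to the proximal blood flow rate"). Aim 1 adds a second pressure measure: "We will also estimate the absolute AVF luminal pressure using the difference between the mean arterial pressure and AVF pressure gradient". Under Aim 3, "the association between pressure values and AVF maturation rates will be analyzed". Aims 2 and 4 relate the same pressures to vessel diameters and to known risk factors.

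For the analysis, section 2.6 names two-sample t tests and a multivariate logistic regression that "will be used to evaluate the association between predictor variables and outcome variables". Technician does not appear among the variables of sections 2.4.1 and 2.4.2 or in section 2.6, and the article describes no repeat reading or agreement check between the two technicians.

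**The concern.** The sentence credits the design with a property that rotation does not supply. Where one technician scans a patient, any systematic difference between the two becomes part of that patient's pressure value. Rotation spreads the difference over the sample but does not remove it. To reveal or remove it, both technicians must scan some of the same patients, or technician must be used in the analysis.

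At stake is the contrast the study is built on, pressure in fistulas that mature against pressure in those that do not. Extra operator variance shrinks the standardised difference and costs power. If one technician happened to scan more of the patients likely to mature, part of the contrast would be an operator effect. The sample size has little slack to absorb a loss, as the first step of the working shows.

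**Working it through.** **1. The plan's own figure.** Inputs from section 2.6: effect size d = 0.6 ("Assuming the effect size to be 0.6"), α = 0.05, power 0.8, allocation ratio 1, and t tests described as two-tailed. With 45 per group the noncentrality is 0.6 × √(45 × 45 / 90) = 0.6 × 4.743 = 2.846, on 88 degrees of freedom with critical value 1.987. Power from the noncentral t is 0.804. With 44 per group it is 0.795, so 45 + 45 = 90 is the smallest balanced total. The stated 90 reproduces exactly.

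**2. Loss of power from an additive operator offset.** Assumptions not in the documents: a between-technician offset of k SDs of pressure; half the scans in each outcome group done by each technician; d = 0.6 free of operator error. The split adds variance k²/4, so the observed effect is d / √(1 + k²/4).

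| Offset k | Added variance | Operator share of total variance | Observed d | Power at N = 90 |
|---|---|---|---|---|
| 0 | 0 | 0% | 0.600 | 0.80 |
| 0.5 | 0.0625 | 0.0625/1.0625 = 5.9% | 0.6/√1.0625 = 0.582 | 0.78 |
| 1.0 | 0.25 | 0.25/1.25 = 20% | 0.6/√1.25 = 0.537 | 0.71 |

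At a 20% operator share, restoring 80% power would take 112 patients.

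**3. Bias, only if technician is associated with outcome.** Suppose one technician scans 60% of the matured and 40% of the failed fistulas. An offset of k SDs then adds (0.60 − 0.40) × k = 0.2k SD to the group difference: 0.1 SD for k = 0.5 and 0.2 SD for k = 1.0. With an equal split the term is zero. The 60/40 figure is only an illustration.

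**4. Does the pressure formula amplify the error?** The equation is not visible in the text at hand. If it has the standard squared form, the gradient is proportional to V₁² − V₂². A proportional error (1 + e) common to both readings then multiplies the gradient by (1 + e)²: 1.05² = 1.10, 1.10² = 1.21, 1.15² = 1.32. The relative error roughly doubles in the gradient.

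For absolute pressure, MAP − G, the relative change is [(1 + e)² − 1] × G / (MAP − G). Take e = 10% and, for illustration, MAP = 100 mmHg:
- G = 12: 0.21 × 12 / 88 = 2.52/88 = 2.9%.
- G = 32: 0.21 × 32 / 68 = 6.72/68 = 9.9%.

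Neither reaches 21%, so the doubling does not simply carry over to absolute pressure.

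**5. What a technician term can do.** If the observed pressure is the true pressure plus δT, with T = 0 or 1 for technician, then β × true pressure = β × observed pressure − βδT. A two-level term absorbs βδT exactly. If the error is a multiplier, the slope itself differs by technician and the term corrects only part of it.

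**The case against.** Several points on the other side are sound.

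- **The article is a condensed account.** Operator identity, cross-training and covariate lists are often left to a fuller document. A reader might infer that the investigators do not plan to record or use technician. The article does not support that; it only fails to describe it, and section 2.6 does not close the list of predictors. The finding rests on the stated rationale, which remains wrong whatever else is written elsewhere.
- **A fixed pair on one ultrasound system at one hospital limits variability** compared with open staffing. That is true, and it is a fair reason for the arrangement. Limiting operator variation is still less than ensuring consistency.
- **The size is assumed.** No document gives an operator difference or an SD of pressure. The assumed 0.6 may already include operator variance, in which case step 2 counts it twice. At an offset of 0.5 SD the loss is only about two points of power. All of this stands.
- **Bias is conditional.** Scans are done within 1 week and the outcome is assessed by 2 months, so the reading cannot respond to the outcome. A reader might infer that rotation follows the calendar, the surgeon or the type of fistula and so biases the result. The article does not say how technicians are assigned, and nothing in it shows such a link.
- **Squaring is not in the visible text**, which calls both inputs flow rates. Amplification therefore has to stay conditional.

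**Conclusion.** The statement that rotation makes the readings consistent is not correct as written, and no analysis document could make it so. Its consequence is uncertain in size. On the assumptions in step 2, power at 90 patients is 0.78 to 0.71 instead of 0.80; with a smaller operator difference, or if 0.6 already allows for operator variance, the loss is smaller still. With rotation unrelated to case mix the association is attenuated, not biased.

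A reader might go further and conclude that the sample size is wrong or that operator error is certain to double in the exposure. Neither follows: the 90 reproduces exactly, and the doubling needs the squared form, an error common to both readings, and the gradient as the measure. This is a cheap improvement worth making, not a flaw that undermines the study.

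**What to change.** 1. In section 2.4.3, replace the claim about consistency with a plain statement that two technicians perform the scans.
2. Record the technician for every week-1 scan, including scans already done where the scan record shows who performed them.
3. Include technician as a two-level term in the Aim 3 logistic model, or compare pressure between outcome groups within technician.

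Do not move the remaining scans to a single technician. Section 2.3.3 has recruitment running from September 2018 to May 2020, and the article appeared in October 2019. A switch at that stage would leave the earlier scans mixed and tie operator to calendar time.

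The cost is one data field, one model degree of freedom, and the work of retrieving the operator for some earlier scans, a few of which may stay unknown. The term removes an additive shift but not all proportional error.
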